### Data collection

Data is collected through patient interview and abstraction from the medical record. Patient medical and surgical history, preoperative medications, intraoperative medications and events, and postoperative medications, assessments, and events are abstracted from the medical record and stored in a Research Electronic Data Capture (REDCap) application. BIS data are downloaded and saved on a networked server at the end of each operation.

### Baseline and follow-up assessments

Patients undergo assessments prior to surgery and at 3- and 12-months postoperatively as described in Table 1. After surgery, research staff administer assessments in person at the 3-month clinical follow-up appointment, or by telephone in the case that follow-up assessments cannot be coordinated in person. The 12-month assessment is administered by telephone. Retention will be encouraged during each of these visits.

**Table 1 Tab1:** Baseline and Follow-up Standardized Assessments

Neuropsychological Assessments	
Mini-Mental Status Examination ^a^	
Verbal Fluency Trials from the Calibrated Ideational Fluency Assessment	
Trail Making Test ^b^	
Digit Span Forwards/Backwards	
Function, Disability, and Health-Related Quality of Life Assessments	
Instrumental Activities of Daily Living	
Oswestry Disability Index	
12-Item Short Form Health Survey	
Pain scores	

^a^In the case of a telephone interview, the Telephone Interview for Cognitive Status is used

^b^The Trail Making Test is not administered in the case of telephone interview

### In-hospital delirium assessment

Delirium is assessed daily during the first three postoperative days using the Confusion Assessment Method (CAM) [32]. The CAM is a well-validated and standardized method for non-psychiatrists to diagnose delirium, with excellent sensitivity (94–100%) and specificity (90–95%). As part of the CAM assessment, trained study personnel visit the patient daily in the hospital and administer the following tests: Mini-Mental State Examination (MMSE) [33], Calendar Reverse Months, Shortened Digit Span Forward and Reverse, and Delayed Word Recall. Nursing staff, clinicians, and family and/or providers are also approached to provide further information for each patient assessment. Using this information, research staff complete the CAM algorithm. A chart review for delirium is also conducted using validated methods to supplement the in-person assessments [34]. Delirium severity is assessed using the Delirium Rating Scale-Revised 98 [35].

### Primary and secondary outcome

The primary outcome is incident delirium based on any positive Confusion Assessment Method (CAM). The primary secondary outcome is change in MMSE at 3-months after surgery.

### Other secondary outcomes

Additional domains that are important for postoperative recovery will be examined as secondary outcomes. These domains include: duration and severity of delirium, other tests of cognition, functional status, disability, health-related quality of life, health care utilization, and pain. The specific tests and outcomes for each of these domains are listed and defined in Table 2.

**Table 2 Tab2:** Primary and Secondary Outcomes

Domain	Outcome	Definition
Delirium	Incident delirium *(Primary Outcome)*	Any CAM (+) assessment
	Delirium severity	Maximum DRS-R-98 score
	Number of days of delirium	Number of CAM (+) days
Cognition	Change in MMSE/TICS	Change in score. Item response theory will be used to compare similar or exact items if TICS> 50% of responses.
	Change in other individual test scores	Verbal Fluency (all trials combined, sum of scores), TMT-A (time), TMB-B - TMT-A (time), DSF (longest span correct), DSB (longest span correct)
Function	Any decline in IADL score	Any decline in IADL score from baseline to 3- and 12-month follow-up
Disability	Change in ODI score	Change in ODI score (%) from baseline to 3- and 12-month follow-up
Health-Related Quality of Life	Change in SF-12 PCS	Change in PCS score from baseline to 3- and 12-month follow-up
	Change in SF-12 MCS	Change in MCS score from baseline to 3- and 12-month follow-up
Health Care Utilization	Readmissions	% Readmissions
	Emergency department visits	% Emergency department visits
	Duration of hospitalization	Number of days in hospital after surgery
Pain	PACU pain	Last pain score in PACU.
		Total morphine equivalents
		Time to first opoid
	Hospital pain	Last pre-discharge pain score.
		Total morphine equivalents, pro-rated for 72 h in hospital
	Post-discharge pain	Average pain score at 3- and 12-month follow-up

Abbreviations: *CAM* Confusion Assessment Method, *DRS-R-98* Delirium Rating Scale-Revised 1998, *MMSE* Mini-Mental State Examination, *TMT* Trail Making Test, *DSF* Digit Span Forward, *DSB* Digit Span Backwards, *IADL* Instrumental Activities of Daily Living, *ODI* Oswestry Disability Index, *SF-12* 12-Item Short Form Health Survey, *PCS* physical component summary, *MCS* mental component summary, *PACU* postoperative anesthesia care unit

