The most important secondary outcome is change in MMSE (or Telephone Interview for Cognitive Status [TICS]) [37]. Change in MMSE/TICS will be analyzed using linear regression analysis, first unadjusted, and then with adjustment for age and education, with consideration of gender, race, and other variables associated with change in MMSE/TICS in bivariate analyses. If TICS is > 50% of responses, we will use item response theory to compare similar or exact items on the TICS and MMSE. The treatment effect will be defined as the difference in the change in MMSE/TICS at three months comparing the intervention and control groups. Other pre-specified secondary outcomes that will be compared between groups by domain are listed in Table 2 and include: (1) delirium severity and number of days of delirium, (2) change in each individual cognitive test score), (3) change in function, disability and quality of life (Instrumental Activities of Daily Living score [38] [any decline], Oswestry Disability Index score [39], Short Form (SF)-12 Physical Component Summary, SF-12 Mental Component Summary [40], (4) hospital utilization (readmissions, emergency department visits, duration of hospitalization, and (5) pain (pain in the postoperative anesthesia care unit, hospital pain, and post-discharge pain. The main post-discharge outcomes will be measured at 3-months. However, we will also collect and report data at 12-months after surgery. For continuous and binary secondary outcomes, similar methods as described above will be applied. We anticipate that delirium severity and number of days of delirium will be highly skewed and will be analyzed as ordinal or dichotomous variables.

Other pre-specified analyses include examining (1) the association of delirium and hospital utilization and other post-discharge outcomes (2) the association of BIS values and burst suppression with postoperative delirium and cognitive change, and (3) risk factors for decline in cognition, function, or health-related quality of life after spine surgery. In all analyses, a value of *p* < 0.05 will be considered significant. Due to the number of outcomes that will be examined (beyond incident delirium and change in MMSE), the analyses of secondary outcomes will be considered preliminary and hypothesis-generating.

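### Post-discharge pain is defined without a baseline reference, and baseline pain, although collected, is not pre-specified as a covariate; the cost is some precision in a secondary outcome

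*Protocol article*

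**What the plan says.** All places are in the protocol article.

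- **Outcome definition.** Table 2 (Other secondary outcomes) defines post-discharge pain as "Average pain score at 3- and 12-month follow-up".
- **Neighbouring rows.** Disability is "Change in ODI score (%) from baseline to 3- and 12-month follow-up", physical quality of life is "Change in PCS score from baseline to 3- and 12-month follow-up" (the mental component is worded the same way), and function is "Any decline in IADL score from baseline to 3- and 12-month follow-up".
- **Data collected.** Under Baseline and follow-up assessments, "Patients undergo assessments prior to surgery and at 3- and 12-months postoperatively as described in Table 1". Table 1 lists pain scores among these instruments, so a preoperative pain score exists.
- **Time points.** Data and statistical analysis states: "The main post-discharge outcomes will be measured at 3-months". It adds: "However, we will also collect and report data at 12-months after surgery".
- **Method.** The same section says: "For continuous and binary secondary outcomes, similar methods as described above will be applied". The method described above it, for the cognitive change score, is linear regression, first unadjusted and then adjusted for age and education. Gender, race and other variables associated with the outcome in bivariate analyses may also be considered.
- **Status.** Outcomes beyond delirium and MMSE change are labelled hypothesis-generating.

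**The concern.** Post-discharge pain is the only patient-reported follow-up outcome in Table 2 without a baseline reference. In patients having lumbar fusion, preoperative pain is a plausible predictor of later pain, and it is already measured. The definition does not use it, and the carried-over regression does not name it. Baseline pain could therefore enter only as a data-driven choice made after the data are seen. What is at stake is precision, and an avoidable analyst's choice in the adjusted model.

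The wording is a second, smaller problem. The word average has no single meaning here. It could be a patient's rating of average pain at each visit, a group mean, or one mean over the two visits. These lead to different analyses.

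**Working it through.** The article gives no figure for pain, so there is nothing to reproduce. The check has two parts.

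**1. Reading the definitions side by side**

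| Outcome | Baseline collected | Definition refers to baseline |
|---|---|---|
| IADL | yes | yes (any decline) |
| ODI | yes | yes (change) |
| SF-12 PCS, MCS | yes | yes (change) |
| Post-discharge pain | yes | no |

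The recovery-room and pre-discharge pain rows are also raw scores, but those are in-hospital measures. No outcome definition uses baseline pain, and no passage names it as a covariate.

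**2. What the omission costs**

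Inputs:
- 206 evaluable patients (Sample size), allocated 1:1 (Trial design and overview), so 103 per arm.
- Significance level 0.05 and power 0.80 (Sample size). Two-sided testing is assumed.
- The correlation r between baseline and follow-up pain is not in the document. It is assumed, with 0.3 to 0.5 as the working range and 0.2 to 0.7 shown.

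Variance of the treatment contrast, relative to the raw follow-up comparison (= 1):
- adjusted for baseline by regression: 1 − r²
- plain change from baseline: 2(1 − r), taking equal SDs at baseline and follow-up

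Detectable difference in SD units:
- raw: (1.960 + 0.842) × √(2/103) = 2.802 × 0.139 = 0.390
- otherwise: 0.390 × √(variance factor)

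| r | Adjusted: variance | Adjusted: detectable | Change: variance | Change: detectable |
|---|---|---|---|---|
| 0.2 | 0.96 | 0.383 | 1.60 | 0.494 |
| 0.3 | 0.91 | 0.372 | 1.40 | 0.462 |
| 0.5 | 0.75 | 0.338 | 1.00 | 0.390 |
| 0.7 | 0.51 | 0.279 | 0.60 | 0.302 |

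Over r = 0.3 to 0.5, adjustment removes 9% to 25% of the variance. That is worth 1/0.91 = 1.10 to 1/0.75 = 1.33 times the patients for this outcome. Plain change has 40% more variance than the raw score at r = 0.3 and only equals it at r = 0.5. Copying the form of the neighbouring rows would therefore not help in this range.

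The figures use 103 per arm with complete pain data. Missed visits would raise every detectable difference, but the variance ratios would stay the same.

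**The case against.** **The comparison is valid as it stands.** Randomization makes the raw comparison of follow-up scores unbiased. A reader might infer that chance baseline imbalance biases the result. With 103 per arm, the 95% range of that imbalance is ±1.96 × 0.139 = 0.27 SD, which at r = 0.3 to 0.5 corresponds to a shift of 0.08 to 0.14 SD in the contrast. The standard error and confidence interval already allow for this, so it is not an additional error. This objection stands, and the point is about precision only.

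**Baseline pain may still be used.** A reader might infer that it is discarded. The article does not support that: the clause on other variables associated with the outcome leaves room for it, and the full analysis plan is not shown. This stands in part. Selection by bivariate association is not pre-specification, and the covariates that the article does fix are age and education.

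**The visits are probably not pooled.** A reader might infer that the 3- and 12-month scores are averaged, which would halve an effect present only at 3 months and mix one-visit with two-visit values. The article nowhere says this. The other Table 2 rows use the same phrase about the two follow-ups for separate visits, and the analysis section makes 3 months the main time point. Missing values also have a rule: multiple imputation from 5% to below 40% missing. What remains is a wording ambiguity.

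**Differing from the other rows is no defect in itself.** This stands: over r = 0.3 to 0.5 the raw score is at least as precise as plain change.

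**Conclusion.** The point holds as a minor one. Baseline pain is collected, the definition of post-discharge pain does not refer to it, and it is not pre-specified as a covariate. The consequence is avoidable loss of precision: with adjustment, the detectable difference would be 0.372 to 0.338 SD instead of 0.390 SD. This rests on an assumed correlation of 0.3 to 0.5, 103 evaluable patients per arm and two-sided testing. At r = 0.2 the gain is small (0.383 SD); at r = 0.7 it is large (0.279 SD).

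The documents do not support a claim of bias, of baseline pain being excluded from every analysis, or of a lost 3-month time point. The outcome is secondary and hypothesis-generating, and neither the primary outcome nor the MMSE outcome is affected.

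**What to change.** Replace the Table 2 entry, or state in the analysis plan before analysis, that post-discharge pain is the pain score at 3 months (main) and, separately, the pain score at 12 months. Compare each between arms by linear regression with the preoperative pain score as a pre-specified covariate, whatever any bivariate screen shows. State whether the score is a patient's rating of average pain, so that the word average has one meaning. Do not convert the outcome to plain change from baseline, which is less precise than the raw score when r is below 0.5 and less precise than the adjusted analysis throughout the range shown.

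The cost is one or two lines of text and one degree of freedom in the model. No new data are needed.

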### Sample size

Assuming a delirium incidence of 35% in the control and a 50% reduction in the intervention group [2, 20], 206 patients would be needed to show a difference in incidence of delirium at a 0.05 significance level with a power of 0.8. With an estimated 6% withdrawal, the target enrollment is 218 patients. The expected sample size of 206 patients will also be sufficient for the secondary outcome of MMSE change at 3-months after surgery: the minimum detectable change in MMSE with 206 patients is ±0.235 at a 0.05 significance level with a power of 0.8.

### Data and statistical analysis

Data are entered on case report forms with subsequent entry into an on-line database application (REDCap). All paper forms are kept in a locked cabinet and are identified only with a study number. All REDCap databases are password protected and accessible only to authorized users. Data will be exported from REDCap to statistical package software in a SAFE environment for data analyses.

Data will first be evaluated for errors and patterns of missing data. Exploratory data analysis of patient characteristics and outcomes will be conducted, including visualization of the data using tables and graphs. Patients will be compared by group with respect to baseline characteristics collected for the cohort, including age, gender, race, education, comorbidities, medications, and perioperative characteristics, among others.

If the prevalence of missing data is < 5%, then primary analyses will be performed with the complete observed data. Sensitivity analyses will be performed using a best-worst case scenario, where all of those lost to follow-up in one group will be analyzed as having incident delirium and all of those lost to follow-up in the other group will be analyzed as not having incident delirium, and then vice versa; each of these results will then be qualitatively compared to the complete observed data results. If the prevalence of missing data is ≥5% but less than 40%, then multiple imputation methods will be employed; sensitivity analyses will compare the results from the multiple imputation analyses to the complete observed data analyses. If the prevalence of missing data is ≥40%, then analyses will be considered as preliminary and hypothesis-generating.

The primary analysis will be based on intention to treat principles, i.e. patients will be analyzed in the group to which they were randomized. For the primary outcome, incident delirium, both the absolute difference and relative change (i.e. relative incidence) will be computed, and the statistical test will be based on a two-sample test for proportions.

It is expected that < 10% of patients randomized to receive spinal anesthesia will actually receive general anesthesia due to failure to obtain spinal anesthesia. If patients receive both a spinal and general anesthetic, they will be categorized into an appropriate group for the on-treatment approach based on the biologic hypothesis for each analysis. For the purposes of the primary analysis on-treatment approach, they will be considered to have received deep anesthesia.

In a sensitivity analysis, we will consider accounting for crossover based on an inverse-probability of treatment weighting approach. This approach will provide an estimate of the difference in the incidence of delirium comparing the intervention and control groups, had all patients received their randomized treatment. Other sensitivity analyses will include: a) an as-treated analysis, b) re-estimation of both of the above treatment effects after adjustment for select baseline covariates, including age, education, and cognitive score [36], with consideration of gender, race, and other variables associated with incidence of delirium in bivariate analyses, and c) pre-specified subgroup analyses based on stratifying patients by age (< 75 vs. > 75 years old), baseline Charlson Comorbidity Index (0 vs. > 0), and baseline cognition (MMSE < 27 vs ≥27, or lowest quartile vs upper quartiles, dependent upon the baseline distribution). Confidence intervals and *p*-values will be generated via a bootstrap procedure using 5000 bootstrap samples.

The most important secondary outcome is change in MMSE (or Telephone Interview for Cognitive Status [TICS]) [37]. Change in MMSE/TICS will be analyzed using linear regression analysis, first unadjusted, and then with adjustment for age and education, with consideration of gender, race, and other variables associated with change in MMSE/TICS in bivariate analyses. If TICS is > 50% of responses, we will use item response theory to compare similar or exact items on the TICS and MMSE. The treatment effect will be defined as the difference in the change in MMSE/TICS at three months comparing the intervention and control groups. Other pre-specified secondary outcomes that will be compared between groups by domain are listed in Table 2 and include: (1) delirium severity and number of days of delirium, (2) change in each individual cognitive test score), (3) change in function, disability and quality of life (Instrumental Activities of Daily Living score [38] [any decline], Oswestry Disability Index score [39], Short Form (SF)-12 Physical Component Summary, SF-12 Mental Component Summary [40], (4) hospital utilization (readmissions, emergency department visits, duration of hospitalization, and (5) pain (pain in the postoperative anesthesia care unit, hospital pain, and post-discharge pain. The main post-discharge outcomes will be measured at 3-months. However, we will also collect and report data at 12-months after surgery. For continuous and binary secondary outcomes, similar methods as described above will be applied. We anticipate that delirium severity and number of days of delirium will be highly skewed and will be analyzed as ordinal or dichotomous variables.

Other pre-specified analyses include examining (1) the association of delirium and hospital utilization and other post-discharge outcomes (2) the association of BIS values and burst suppression with postoperative delirium and cognitive change, and (3) risk factors for decline in cognition, function, or health-related quality of life after spine surgery. In all analyses, a value of *p* < 0.05 will be considered significant. Due to the number of outcomes that will be examined (beyond incident delirium and change in MMSE), the analyses of secondary outcomes will be considered preliminary and hypothesis-generating.

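### The unadjusted delirium test is valid but leaves collected baseline predictors unused, and the adjusted delirium and MMSE/TICS models add covariates by screening against the outcome

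*Protocol article*

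**What the plan says.** All of this is in the protocol article under Data and statistical analysis.

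- **Primary outcome.** Delirium is analyzed by intention to treat. Absolute and relative differences are computed, and "the statistical test will be based on a two-sample test for proportions". No covariates are used.
- **Adjusted delirium analyses.** These are listed among the sensitivity analyses, as "re-estimation of both of the above treatment effects after adjustment for select baseline covariates, including age, education, and cognitive score". The sentence then widens the set, "with consideration of gender, race, and other variables associated with incidence of delirium in bivariate analyses". Confidence intervals and p-values come from a bootstrap with 5000 samples.
- **Main secondary outcome.** Change in MMSE/TICS is analyzed by linear regression, first unadjusted and then adjusted for age and education, "with consideration of gender, race, and other variables associated with change in MMSE/TICS in bivariate analyses". The word baseline does not appear in this rule.
- **Status of the results.** The threshold p < 0.05 applies to every analysis. Secondary outcomes are called hypothesis-generating, but incident delirium and change in MMSE are outside that label.
- **Description of the cohort.** The characteristics to be compared between groups at baseline include "comorbidities, medications, and perioperative characteristics, among others".

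**The concern.** There are two separate issues.

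**Unused precision.** The plan already treats age, education and cognitive score as worth adjusting for, and all three are known before randomization. The primary test uses none of them. Under Strengths and limitations, the article says that the trial may be underpowered and that control incidence may be nearer 22–26% than 35%.

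**Covariates chosen by the outcome.** A variable enters the adjusted models because it is associated with the outcome in the trial's own data. Each outcome can therefore acquire its own covariate set, known only once the outcome data have been examined. For MMSE/TICS nothing confines the screen to pre-randomization variables. The Data collection section lists intraoperative medications and events, postoperative medications and events, and BIS recordings. Several of these are consequences of the assigned anesthetic, and adjusting for one that lies on the path to cognition would remove part of the effect being estimated.

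**Working it through.** **1. Does the stated sample size match the unadjusted test?**

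Inputs from the Sample size section: "Assuming a delirium incidence of 35% in the control and a 50% reduction in the intervention group", so p1 = 0.35 and p2 = 0.175; and "206 patients would be needed to show a difference in incidence of delirium at a 0.05 significance level with a power of 0.8", so n = 103 per arm at 1:1. Two-sided testing is assumed.

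Mean p = (0.35 + 0.175)/2 = 0.2625, and 0.2625 × 0.7375 = 0.1936. Sum of arm variances: 0.35 × 0.65 + 0.175 × 0.825 = 0.2275 + 0.1444 = 0.3719.

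Power = Φ{[0.175 − 1.96 × √(2 × 0.1936/103)] / √(0.3719/103)} = Φ{(0.175 − 0.1202)/0.0601} = Φ(0.91) = 0.819.

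The same pooled formula solved for 80% power gives 99 per arm, 198 in total; with a continuity correction it gives 220. The stated 206 lies between these. It is consistent with an unadjusted test and is not an error.

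**2. What could adjustment add?**

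The documents give no prognostic strength, so the share of outcome variance explained (R²) is an assumption. Adjustment acts roughly like replacing n by n/(1 − R²) in the formula above.

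| Assumed R² | Effective n per arm | Power, 35% v 17.5% | Gain (points) |
|---|---|---|---|
| 0 | 103.0 | 0.819 | – |
| 2% | 105.1 | 0.827 | 0.8 |
| 5% | 108.4 | 0.838 | 1.9 |
| 10% | 114.4 | 0.858 | 3.8 |
| 15% | 121.2 | 0.877 | 5.8 |

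With unpooled variance, 0.830 rises to 0.848–0.885 for R² of 5–15%.

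For a halving from the control rates that the article itself mentions, pooled power without adjustment is 0.655 (26% v 13%) and 0.567 (22% v 11%). R² of 5–15% raises these to 0.678–0.727 and 0.589–0.637.

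**3. Simulation: unadjusted, fixed list, screened list.**

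Settings: 206 patients, 4000 runs, 35% v 17.5% for power and 35% in both arms for type I error. The adjusted analyses use a risk difference standardized from a logistic model. The screen adds any of 12 pure-noise candidates with bivariate p < 0.10; both of those numbers are assumed. The first column is the standard deviation of the covariate part of the linear predictor.

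| SD | Power: unadjusted | Power: three fixed covariates | Power: fixed plus screened | Type I: unadjusted | Type I: fixed | Type I: screened | Type I: any of the three significant |
|---|---|---|---|---|---|---|---|
| 0 | 82.1% | 81.9% | 81.3% | 5.4% | 5.9% | 5.9% | 6.9% |
| 0.6 | 81.7% | 84.2% | 83.4% | 4.8% | 5.2% | 5.3% | 7.0% |
| 1.0 | 82.5% | 88.0% | 87.6% | 4.8% | 5.2% | 5.4% | 7.7% |
| 1.4 | 81.6% | 90.5% | 90.0% | 5.0% | 5.6% | 5.5% | 7.9% |

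The unadjusted test keeps its size. The fixed list gains between nothing and about 9 points. Screening is 0.4–0.8 points below the fixed list in power, and its type I error is practically the same. The error rises to about 7–8% only if whichever of the three results is significant gets reported.

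**4. Can post-randomization variables enter?**

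For delirium, the screening phrase continues a clause about select baseline covariates, so its natural reading is baseline only. For MMSE/TICS no such limit is stated.

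**The case against.** - **An unadjusted primary test with adjusted sensitivity analyses is a coherent choice.** This stands. The test is valid under randomization, the article describes no stratification factors that it would ignore, and the sample size fits it. The case for adjustment is efficiency alone.
- **The gain is assumed and may be small.** This also stands. Excluding dementia and MMSE < 24, and enrolling only from age 65, narrows two of the three predictors.
- **For delirium, the screen affects only sensitivity analyses.** Correct. A reader might infer that the primary p-value can be steered by covariate choice; it cannot, because the primary test is fixed.
- **Over-adjustment.** A reader might take the mention of perioperative characteristics as defining the pool for the delirium models. That sentence concerns a descriptive comparison of groups, and the delirium models refer to baseline covariates. The risk survives only for MMSE/TICS.
- **Standard errors.** A reader might infer that they will be too small because selection is ignored. The article plans a bootstrap for the sensitivity analyses and does not say whether selection is repeated in each resample, so the text does not support that inference. The simulation found no material inflation from screening alone.
- **Masking.** Analysts will be masked, which limits deliberate steering. It does not make the covariate set independent of the outcome data.
- **A separate analysis plan may give the details.** A missing threshold or candidate list would be no finding. But the article itself states the outcome-driven rule, twice, and a plan with a fixed list would have to replace that wording.

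**Conclusion.** The point holds as a low-cost improvement. It does not show that the primary analysis is invalid.

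- **Precision.** At the design rates, adjustment for the three named covariates is worth about 1 power point at R² = 2% and about 2–6 points at 5–15%. The size rests wholly on that assumed R² and could be near zero.
- **Screening.** It makes the covariate set depend on the outcome data and, in the simulated setting of noise candidates, gains no power over a fixed list. It matters most for MMSE/TICS. That outcome is exempt from the hypothesis-generating label, is judged at p < 0.05, and has a covariate pool not limited to baseline, so variables affected by the anesthetic could enter.

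**What to change.** **For the randomized (intention-to-treat) comparisons:**

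1. Delete both clauses that admit covariates by bivariate association with the outcome.
2. Fix one list of pre-randomization covariates before unmasking: age, education and baseline MMSE.
3. For delirium, report the risk difference and risk ratio standardized from a logistic model with that list, with robust or bootstrap standard errors. Make this the primary estimate or, if the sponsor keeps the unadjusted test as primary, the single named supportive analysis. Show the raw 2x2 result either way.
4. Use the same list in the adjusted MMSE/TICS regression. This adds baseline MMSE to the age and education already named there.

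**For the as-treated and crossover-weighted analyses:** these are not protected by randomization, and a short list chosen for precision may under-adjust them. Give them their own pre-specified set of pre-randomization confounders.

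**Cost:** analysis wording only, with no new data and no change to the sample size. If the adjusted estimate becomes primary, the headline figure comes from a model rather than a raw table, which is why both should be shown.

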### Eligibility criteria

Inclusion criteria for participation in the study are: 1) age 65 years or older, 2) undergoing a lumbar spine fusion surgery, 3) expected duration of surgery < 3 h, 4) under the care of a participating surgeon, and 5) expected ability to understand and comply with study procedures. Exclusion criteria are: 1) contraindications to spinal anesthesia (e.g. severe aortic stenosis, anti-coagulant or anti-platelet therapy), 2) BMI > 40, 3) prior L2–5 full lumbar fusion, 4) communication issues precluding baseline assessments, 5) baseline dementia or MMSE < 24, 6) psychiatric disease that would preclude cooperation with sedation with spinal anesthesia, and 7) attending surgeon or anesthesiologist preference for either spinal or general anesthesia for any reason due to clinical considerations.

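### The age subgroups leave out patients aged exactly 75, and subgroup p-values count as significant with no stated interaction test

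*Protocol article*

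**What the plan says.** In the Protocol article, section Data and statistical analysis, subgroups are the third item in a list of further sensitivity analyses, which begins "pre-specified subgroup analyses based on stratifying patients by age". Three factors are named:

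- Age: "stratifying patients by age (< 75 vs. > 75 years old".
- Comorbidity: "baseline Charlson Comorbidity Index (0 vs. > 0".
- Cognition: "baseline cognition (MMSE < 27 vs ≥27, or lowest quartile vs upper quartiles, dependent upon the baseline distribution".

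The next sentence says that confidence intervals and p-values "will be generated via a bootstrap procedure using 5000 bootstrap samples". Later in the same section, a p-value "< 0.05 will be considered significant" in every analysis. The caution that results are exploratory is worded for the secondary outcomes, because of their number. It does not mention subgroups of the primary outcome. No interaction test is named.

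Under Eligibility criteria, patients with "baseline dementia or MMSE < 24" are excluded, so the lower MMSE stratum can hold only scores 24 to 26. Under Masking, statisticians and investigators who analyse the data are masked.

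**The concern.** **Age boundary.** With age in whole years, the rule has no place for a 75-year-old. The other splits in the same sentence (0 against above 0; below 27 against 27 or more) are exhaustive. Followed literally, the rule drops randomised patients from an analysis that is called pre-specified. If it is left alone, someone must assign them later, when data exist.

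**Inference.** The article fixes p-values and a 0.05 threshold for the stratified analyses but does not say which quantity supports a claim that the effect differs between strata. A significant result in one stratum and a non-significant one in the other is not evidence of such a difference. At this sample size the pattern is common even when the effect is identical. The risk is a report that the technique works only in, say, older patients.

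**Working it through.** **Inputs.** Control rate 35%, halved to 17.5%; 206 evaluable patients; alpha 0.05 and power 0.8 (Sample size); 1:1 allocation (Trial design and overview); lower control rates of 22-26% that the article itself considers (Strengths and limitations). Assumptions: two-sided testing, stratum sizes, and the share of patients aged 75.

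**1. The plan's own figure.** With n per arm, power = Φ((Δ − 1.96·s0)/s1), where s0 = √(2p̄(1−p̄)/n) and s1 = √((p1q1 + p2q2)/n). For n = 103, Δ = 0.175 and p̄ = 0.2625: s0 = 0.0613, s1 = 0.0601, and power = Φ((0.175 − 0.1202)/0.0601) = Φ(0.91) = 0.82. The stated 0.80 with 206 patients is met.

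**2. Age gap.** 206 × 0.03 = 6.2 and 206 × 0.07 = 14.4, so about 6-14 patients.

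**3. Comparing stratum p-values, same effect in both strata.** Let a and b be the power in the two strata. P(exactly one significant) = a(1−b) + b(1−a). Power is by exact enumeration of the pooled two-sample z test.

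| True rates | Per arm in the two strata | a, b | Exactly one significant |
|---|---|---|---|
| 35% v 17.5% | 51 / 51 | 0.530, 0.530 | 2 × 0.530 × 0.470 = 0.498 |
| 35% v 17.5% | 75 / 28 | 0.690, 0.319 | 0.690 × 0.681 + 0.319 × 0.310 = 0.569 |
| No effect | any | 0.05, 0.05 | 2 × 0.05 × 0.95 = 0.095 |

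The normal approximation agrees closely: 0.524 per stratum and 0.499 discordant for equal halves. With 25% v 12.5% it gives 0.465 for equal halves and 0.507 for a 75/25 split, so the result does not depend on the optimistic control rate.

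**4. Interaction test, same effect in both strata.** A simulation used 10,000 trials of 206 patients, three independent binary factors and a Wald test on the difference in risk differences. It rejects in about 5-6% of trials per factor, and in about 15-16% for at least one of three factors. In the same trials at 35% v 17.5%, at least one factor shows exactly one significant stratum in about 76-79%.

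**5. Power of the interaction test.** Take a risk difference of 17.5 points in one half and 0 in the other, with 51.5 per arm in each half. SE = √((0.35×0.65 + 0.175×0.825 + 2×0.35×0.65)/51.5) = 0.127. Power = Φ(0.175/0.127 − 1.96) = Φ(−0.58) = 0.28.

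**The case against.** The strongest objection is that the article is silent on interaction testing, and a condensed article may leave that to the analysis plan. A reader might infer that the plan is to re-estimate and test within each stratum. The text does not say so: re-estimation belongs to the preceding item, on covariate adjustment, and the subgroup item speaks only of stratifying. The bootstrap p-values could refer to stratum effects or to a difference between them. The 50-57% figures are therefore conditional on a practice that the article does not announce. Subgroups are also listed as sensitivity analyses, and the limitations section says that any finding of benefit would need replication. All of this stands. What remains is that the article does fix p-values and a universal threshold, while its exploratory label does not reach these subgroups.

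A reader might also infer that the MMSE cut is chosen to suit the results, since the alternative is "or lowest quartile vs upper quartiles, dependent upon the baseline distribution". The documents do not support that. Both cuts are named, the choice depends on baseline data, and the analysts are masked; such a choice does not inflate type I error. The quartile option also has a purpose, because scores 24 to 26 may form a very small stratum. The residue is small: no criterion or time for the choice is given, and the section puts exploratory analysis of patient characteristics and outcomes together at the start.

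The age gap looks like a drafting slip and does not touch the primary analysis. It is still a wrong rule as written.

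**Conclusion.** The point holds in limited form.

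- **Age strata:** an error on the face of the article, if age is in whole years. It is small, about 6-14 of 206 patients under the assumed 3-7%.
- **Inference:** a weakness in what is fixed, not a stated wrong method. If stratum significance were compared and the planned effect were the same in both strata, about 50-57% of trials would show exactly one significant stratum per factor, against about 5-6% for an interaction test. With no treatment effect the figure is about 10%. A figure of 26% for any of six stratum tests being significant (1 − 0.95⁶ = 0.265) assumes independence. The three splits reuse the same patients, and simulation gives 21-22%.
- **MMSE cut:** no inflation of error. A note on timing is enough.

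The discordance figures follow from comparing stratum p-values only. Neither the age gap nor the MMSE option produces them.

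**What to change.** 1. Write exhaustive age strata, for example below 75 against 75 or older.
2. State that each subgroup conclusion rests on the treatment-by-subgroup interaction, reported as the difference in risk differences with a 95% CI. Show stratum estimates with CIs.
3. Extend the exploratory label to the subgroup analyses of the primary outcome.
4. Keep both MMSE options if wanted, but settle the choice before outcomes are examined.

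The cost is a few sentences, with no new data and no change to sample size. The downside is low interaction power, about 28% for 17.5 points in one half and none in the other. The plan should say so, so that a non-significant interaction is not read as proof of a uniform effect. Three interaction tests at 0.05 still give about a 15-16% chance of at least one false positive, which is a further reason for the exploratory label.
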